## Abstract

**Methods::**

This single-arm, open-label, pilot intervention study will investigate the efficacy and safety of electrocautery ablative therapy using high-frequency medical devices. Patients diagnosed with grade 2 or 3 AIN will be included and will receive ablation treatment. Then, they will be followed up at 3 and 6 months after the procedure for HRA-guided sextant biopsy. To reduce the possibility of missed lesions before and after the intervention, we will perform HRA-guided sextant biopsy routinely. In this study, a sextant biopsy is defined as at least 6 biopsies in all directions, regardless of abnormal findings under HRA. The primary outcome is the recurrence rate at 6 months, and the secondary outcomes are the adverse event and recurrence rates at 3 months.

**Conclusion::**

This pilot study will provide data on the effectiveness and safety of electrocautery ablation as a treatment for grade 2 or 3 AIN.

## 1. Introduction

Anal cancer is a human papillomavirus (HPV)-associated cancer. More than 90% of anal cancers are caused by HPV, and most of them are HPV16 and 18.^[1]^ The annual incidence of anal cancer in the general population is as low as 1.4 per 100,000 person-years but has remarkably increased by 2.7% per year over the decades.^[2]^ In addition, the at-risk population was reportedly people living with HIV (PLWH), men who have sex with men (MSM), women with HPV-related cancer or precancerous lesions, people with immunosuppression, and smokers.^[3]^ Therefore, a higher incidence of 84 per 100,000 person-years for HIV-positive MSM, which was the highest risk factor, was reported.^[3]^ The prevention of anal cancer is an essential part of anal cancer management because poor prognosis is associated with cancer diagnosis at a more advanced stage.^[4]^

Anal cancer is preceded by high-grade squamous intraepithelial lesion (HSIL), which comprises grade 2 or 3 anal intraepithelial neoplasia (AIN). HSIL in PLWH progresses to cancer at the rate of 402 per 100,000 person-years.^[5]^ At present, a screening program with anal cytology and HPV genotyping is recommended in some at-risk populations based on expert opinion.^[4,6,7]^ Recently, the ANCHOR study conducted in the United States with a large sample size demonstrated that the use of a screening program with interventions for PLWH with HSIL decreased the rate of progression to anal cancer by 57%.^[5]^ In this study, interventions included electrocautery ablation, infrared coagulation, excision, and topical agents, but electrocautery ablation was used most often (83.6%). Electrocautery ablation may be a primary method, as it is an easy, fast, and office-based procedure. Previous studies have shown that electrocautery ablation is effective for treating HSIL with few adverse events.^[5,8,9]^ However, relapse at approximately 1 year after the procedure is a primary concern. The rate of relapse is 25% to 61%; therefore, recurrent procedures may be required for relapsed lesions.^[8,10]^

In Japan, a screening program using high-resolution anoscopy (HRA) is not well established because HRA is available at only a few hospitals for research purposes. Moreover, no treatment options have been approved by the National Insurance for people with HSIL. However, screening with HRA showed that 73.1% (31/52) of participants had HSIL among PLWH, as a previous study showed.^[11]^ These screening programs, followed by effective interventions need to be introduced on priority.

Surgitron, is a popular medical device used for tonsillectomy, eye disease, and anorectal diseases.^[12–15]^ The device provides a high radio frequency for precise ablation that is effective only for targeted lesions and minimizes unintended invasion, leading to few side effects. However, there have been no studies on the treatment of HSIL using this device. Therefore, this pilot study aims to investigate the effectiveness and safety of electrocautery using the Surgitron dual EMC.

## 2. Methods

### 2.1. Ethics statements

This study was approved by the Certified Review Board of National Center for Global Health and Medicine (NCGM-C-004310-00). This trial was registered in the Japan Registry of Clinical Trials (Clinical Trial Plan Number: jRCTs032210649).

The current research protocol is version 1.1, dated October 21, 2021. The principal investigator will prepare an explanatory document, consent document, and consent withdrawal form, which shall be approved by a clinical research review committee approved by the NCGM. The consent document will be prepared for clinical research. The consent document must be prepared in plain language so that it can be understood by the participant in the clinical research (a person who is independent of the person who conducts the clinical research). Persons involved in this research will not obtain personal information through deception or other wrongful means, will make utmost efforts to protect the personal information and privacy of the clinical research participants, and will not divulge personal information obtained in the course of conducting this research without justifiable reason (the same shall apply even after the persons involved leave their positions). In addition, those involved in this research must not handle personal information obtained in the course of conducting the research beyond the scope of consent obtained in advance from the participants of the clinical research. When handling personal information, the principal investigator must specify the purpose of use as much as possible and must keep personal information accurate and up to date to the extent necessary to achieve the purpose of use. They must also take necessary measures to prevent leakage, loss, or damage of personal information and for other appropriate management of personal information, and must specifically stipulate the methods of such measures in the Implementation Rules.

### 2.2. Study design and population

The single-arm, open-label, pilot intervention will investigate the efficacy and safety of electrocautery ablative therapy with the Surgitron for patients with grade 2 or 3 AIN. The study will be conducted in the outpatient clinics of the AIDS Clinical Center and sexual health clinic at the National Center for Global Health and Medicine (NCGM). Staff at the AIDS Clinical Center will provide HIV-infected patients with medical care and treatment. Staff at the sexual health clinic will follow-up high-risk MSM without HIV and regularly assess their HIV status and other sexually transmitted infections. In total, 20 patients with grade 2 or grade 3 AIN will be included in the study for electrocautery ablation and follow-up biopsy with HRA. For sample size calculation to detect a safety problem, a pilot study sample size of 20 has a probability of at least 0.9 that a problem will occur in at least one of the participants. This assumes that each individual has a probability of 0.1 of exhibiting the problem.

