#### 2.3.3. Adverse events

Potential adverse events related to electrocautery ablation include bleeding, textural changes at the targeted lesions, and mild-to-moderate pain for up to 2 weeks after the intervention. Potential rare adverse events (<1%) include heavy bleeding, stenosis, fissure, fistula, and abscess.^[5]^

All serious adverse events occurring between the time informed consent was signed and the end of the trial will be documented in the medical records and reported to the Clinical Research Review Committee.

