### 2.6. Statistical analysis plan

The population to be analyzed is defined as all patients receiving electrocautery ablation. The characteristics of the study participants will be summarized using descriptive statistics. The recurrence rate at each visit will be estimated using point estimates and 95% confidence intervals. The safety analyses will be based on this analysis set. Adverse events will be stratified according to the patients’ HIV status and severity. Analyses will be categorized and aggregated by patient ID, and a list of outcomes will be generated. Data will be analyzed with STATA, version 16.0, and the sample size calculation will be determined using PASS 2022.

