## 3. Discussion

The detection of AIN by screening is key to the prevention of anal cancer. Based on the similarity of cervical cancers, screening programs with interventions such as electrocautery ablation may be a favorable approach in high-risk populations. The ANCHOR study showed that interventions in patients with HSIL significantly reduced the risk of anal cancer. Electrocautery ablation is a promising intervention, particularly when the targeted area is extensive. Several studies have suggested high efficacy and low side effects.^[5,8,10]^ The major concern is the high rate of relapse, and according to previous studies, most recurrences occurred outside of the treated area.^[8,10]^ In our protocol and routine practice for HRA-guided biopsy, biopsy will be conducted in all directions regardless of HRA findings; thus, the results of this study will reflect an accurate clinical course based on pathological findings. This is the big difference between our study and other previous studies.^[5,8,10]^ Furthermore, in this study, the Surgitron dual EMC will be used for electrocautery, and the device has a high radiofrequency, which is expected to reduce postoperative discomfort, scar tissue formation, and enhanced healing while maintaining high efficacy.^[12]^

Several potential limitations of this study need to be acknowledged. First, the study is not a randomized controlled trial or single-arm trial. Therefore, the effectiveness of electrocautery ablation using the Surgitron dual EMC compared with another device is unknown. However, this study will evaluate safety first. Second, since this is a single-arm study with a small sample size, the result will likely be affected by selection biases. Third, the study population will include MSM with and without HIV. Other important at-risk populations include women with HPV-related cancer or precancerous lesions, people with immunosuppression, and people taking immunosuppressants who will not be included in this study. Further studies are needed to overcome these limitations.

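### Section 2.2 overstates what 20 patients deliver: at a per-patient risk of 0.1, the chance of seeing a safety problem at least once is 0.878, not 0.9 or more

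*Protocol article*

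**What the plan says.** Section 2.2 of the protocol article fixes enrolment: "In total, 20 patients with grade 2 or grade 3 AIN will be included in the study". It justifies that number on safety grounds alone, stating that "a pilot study sample size of 20 has a probability of at least 0.9 that a problem will occur in at least one" participant. The next sentence gives the condition: "This assumes that each individual has a probability of 0.1 of exhibiting the problem". Section 2.6 adds that "the sample size calculation will be determined using PASS 2022" and sets the analysis population: "The population to be analyzed is defined as all patients receiving electrocautery ablation". The article gives no power or precision figure for the recurrence endpoint, so the safety statement is the only numerical support offered for 20 patients. The Discussion, where it concedes that there is no comparison with another device, says: "However, this study will evaluate safety first".

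**The concern.** The sentence claims a lower bound on a probability and supplies both quantities needed to compute it. The computed value falls below the bound, so the design does not have the property claimed for it.

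The effect is limited but real. The Discussion puts safety first, and this is the one number that tells a reader how well the trial can reveal a safety problem. As written, it slightly overstates that ability. Anyone who reuses the sentence to size a later pilot would carry the error along.

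**Working it through.** **Inputs**, all from section 2.2: n = 20 patients; per-patient risk p = 0.1; claimed probability of one or more occurrences, 0.9 or higher. The calculation treats patients as independent with a common risk, which is the usual reading of such a statement. Significance level, sidedness and allocation do not enter.

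**1. The plan's own figure.**
P(at least one) = 1 − (1 − p)^n = 1 − 0.9^20 = 1 − 0.1216 = 0.8784.
The stated bound is not reproduced. The shortfall is 0.900 − 0.878 = 0.022, and the probability of seeing no case is 12.2%.

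**2. An alternative formula.**
The Poisson approximation with mean 20 × 0.1 = 2 gives 1 − exp(−2) = 0.865. This is lower still, so it does not explain the stated figure.

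**3. What would make the statement true.**
- Solving for n at p = 0.1: ln(0.1)/ln(0.9) = 21.85, so 22 patients. Check: 21 patients give 0.8906 and 22 give 0.9015.
- Solving for p at n = 20: 1 − 0.1^(1/20) = 0.1087, or about 0.109.

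**4. Dependence on complete follow-up.**
The value 0.878 assumes that all 20 patients are treated and assessed for adverse events. As an illustration, 19 assessed patients would give 0.865 and 18 would give 0.850. The article states no attrition figure, so these are not predictions.

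**5. Context only.**
For any single harm with a risk of 1%, 1 − 0.99^20 = 0.182.

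**The case against.** The strongest defence is proportion. The value 0.878 rounds to 0.9 at the one-decimal precision that section 2.2 uses, and 22 patients is only two more than planned. The statement is a planning remark in a pilot, not a hypothesis test or a stopping rule. Nothing in enrolment, endpoints, analysis set or estimation depends on it. All of this stands, and it makes the point minor. It does not make the sentence correct: the wording sets a floor, and 0.878 lies below that floor. The reference to PASS 2022 does not help either, since no software setting changes a result fixed by the two stated inputs.

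A reader might infer something stronger, namely that the sample size statement misrepresents the trial's ability to detect serious harms. Section 2.3.3 says "Potential rare adverse events (<1%) include heavy bleeding, stenosis, fissure, fistula, and abscess", and 20 patients have only a small chance of showing any one of these. The article does not support that inference as a charge of error, for three reasons.

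- Section 2.2 conditions its claim explicitly on a risk of 0.1 and never extends it to rarer events. Low sensitivity to events under 1% is a property of any study of this size.
- Section 2.3.3 also names bleeding, textural change and pain without the rare label. A planning risk of 10% is a reasonable choice when screening for problems that are not rare.
- The 0.182 figure is a ceiling for one harm, or for all five together only if the 1% is their combined rate, which the article does not say. If the five were independent and each just under 1%, the chance of seeing at least one of any kind could approach 1 − 0.99^100 = 0.634.

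Nor is there a safety conclusion in sections 3 or 4 to restrict. Both describe work still to be done, and the Discussion already acknowledges the small sample.

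**Conclusion.** The stated probability is wrong on the article's own inputs: 0.878 against a claimed minimum of 0.9, a shortfall of 2.2 percentage points. The result rests on independent patients with a common risk of 0.1 and on all 20 being assessed for adverse events. The conclusion does not depend on any document not shown, because the risk, the sample size and the claimed probability all stand in section 2.2.

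Severity is minor. The figure should be corrected because it is false as worded and is the only operating characteristic given for the sample size, but the design does not need to change. The low probability of observing harms under 1% describes what a 20-patient study can show and is not a further fault in the plan.

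**What to change.** Keep 20 patients and restate the sentence in section 2.2, for example:

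> With 20 patients, the probability of observing a safety problem in one or more of them is about 0.88 if the per-patient risk is 0.1 (0.90 if the risk is 0.109).

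Raising enrolment to 22 would also make the existing claim true, but that is not needed for a pilot with no decision rule attached. If the authors wish, they can add that any single harm with a risk of 1% would be seen at least once with probability of about 0.18. This is optional.

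The cost is one edited sentence and a slightly less favourable figure, with no extra patients and no change to conduct or analysis.

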#### 2.2.1. Participant recruitment

The participants will be recruited from the center hospital of the NCGM. The study will be explained to the participants by their primary physician, and they will be asked to sign a consent form.

#### 2.2.2. Inclusion criteria

Patients who meet the following criteria will be eligible to participate in the study.

Persons or their legal representatives who provide written consent for the participation of the patient in the trial.Persons aged 20 years of age or older at the time consent was obtained.Persons diagnosed with grade 2 or 3 AIN based on sextant biopsy results under HRA within 1 year. Sextant biopsy is defined as at least 6 samples in all directions, regardless of abnormal findings.

#### 2.2.3. Exclusion criteria

Patients who meet any of the following criteria will not be eligible to participate in the study.

Persons with invasive cancer.Persons whom the principal investigator, investigator, or sub-investigator judge to be ineligible for other reasons.Pregnant or breastfeeding women.

#### 2.2.4. Study protocol

Table 1 shows the study schedule. A physician will explain the study protocol to each candidate, and if consent is obtained, the physician will ask the candidate to sign an informed consent form and perform the examination in keeping with the description in Table 1. At visit 1, patients with AIN will undergo electrocautery ablation. At visits 2 and 3, a physician will confirm adverse events due to the intervention and perform HRA with a biopsy.

**Table 1 T1:** Study schedule.

	Screening	Visit 1 (day 1)	Visit 2 (day 90)	Visit 3 (day 180)
			±45 days	± 45 days
Informed consent	x			
Confirmation of eligibility (inclusion and exclusion criteria)	x			
Enrollment	x			
Clinical characteristics	x			
Vital signs		x	x	x
Physical findings	x	x	x	x
Electrocautery ablation		x		
Adverse events		x	x	x
High-resolution anoscopy			x	x
Tissue biopsy			x	x

### 2.3. Intervention

#### 2.3.1. Electrocautery ablation

The patient will be placed in the left lateral recumbent position and an anoscope will be inserted to magnify the anal canal for colposcopy. Then, we will apply 3% acetic acid to observe the nebulous anal TZ (aceto-white lesion) surface, margins, and vascular abnormalities, and together with the results of HRA guidance, the ablation area for biopsy will be determined. The targeted area with 3 to 5-mm margins will be ablated with a 4-MHz radiofrequency device (Surgitron; Ellman Japan, Inc., Osaka, Japan). This device offers precise ablation of the targeted area and minimizes postprocedural pain.^[14,15]^ When lesions are extensive, staged ablations are allowed at the physician’s discretion. The second procedure will usually be performed within 3 months.

#### 2.3.2. Follow-up biopsy at visits 3 and 6

The patient will be placed in the left lateral recumbent position, an anoscope will be inserted to magnify the anal canal for colposcopy, 3% acetic acid will be applied, and the aceto-white lesion surface, margins, and vascular abnormalities will be observed. Sextant biopsy samples will be collected in all directions, regardless of abnormal findings, to investigate local and metachronous recurrences.

#### 2.3.3. Adverse events

Potential adverse events related to electrocautery ablation include bleeding, textural changes at the targeted lesions, and mild-to-moderate pain for up to 2 weeks after the intervention. Potential rare adverse events (<1%) include heavy bleeding, stenosis, fissure, fistula, and abscess.^[5]^

All serious adverse events occurring between the time informed consent was signed and the end of the trial will be documented in the medical records and reported to the Clinical Research Review Committee.

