### 2.5. Data collection and management

A case report form (CRF) will be prepared by appropriate and authorized individuals (investigators and physicians). Unless data recorded directly in the CRF are used as the source material, all data recorded in the CRF must be consistent with the original material. During the course of the study, the investigator will collect data at each visit. All study findings and documents will be kept strictly confidential, and patients will be identified only by their patient number and/or birth date, never by name. To protect participant anonymity, the investigator will keep patient-identifying documents confidential.

The following data will be collected.

Date of birth (age), sex, nationality, race, prior medical history, history of current disease, complications, allergy, and pregnancy status;Body weight and height at the first visit;Vital signs at every visit;Level of consciousness;Body temperature (°C);Blood pressure (mm Hg);Pulse rate (beats/min);Respiratory rate; andPhysical condition at every visit (Physical conditions will be examined by inspection, palpation, auscultation, and percussion.).

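### No adverse-event assessment is scheduled between the ablation day and Visit 2 (day 45 to 135), so short-lived non-serious harms, chiefly pain, are likely to be under-recorded

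*Protocol article*

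**What the plan says.** Section 2.3.3 lists the expected harms of the procedure: "Potential adverse events related to electrocautery ablation include bleeding, textural changes at the targeted lesions" and, in the same sentence, "mild-to-moderate pain for up to 2 weeks after the intervention". It also names rarer complications, such as stenosis, fistula and abscess.

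On timing, section 2.2.4 states "At visit 1, patients with AIN will undergo electrocautery ablation" and then "At visits 2 and 3, a physician will confirm adverse events due to the intervention". The adverse-event row of Table 1 is marked at Visit 1 (day 1), Visit 2 (day 90 ± 45 days) and Visit 3 (day 180 ± 45 days), and nowhere else. Section 2.5 fits this: "During the course of the study, the investigator will collect data at each visit".

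Serious events have a continuous rule in section 2.3.3: "All serious adverse events occurring between the time informed consent was signed and the end of the trial will be documented in the medical records".

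On the role of safety, Table 2 makes the occurrence of adverse events the safety endpoint without restricting it to serious ones. Section 2.6 breaks the events down by HIV status and severity. Section 2.2 justifies the 20 patients by the chance of seeing a safety problem. The Discussion says "However, this study will evaluate safety first".

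**The concern.** The article's account of when harm is expected and its timetable for looking for harm do not meet. The one harm with a stated duration lasts at most two weeks, and no visit, call or diary is shown in that period. A patient with a week of moderate pain, or minor bleeding on day 5, would first be asked about it at a scheduled study visit between about 6 and 19 weeks after the procedure. By then whether it happened, how bad it was and how long it lasted must be reconstructed.

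Mild and moderate events make up the lower grades of a severity table. If they are under-recorded, the adverse-event rate is too low and the severity breakdown is distorted, in a pilot whose size and stated priority rest on safety. Once the two weeks have passed, the information cannot be recovered at the analysis stage.

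**Working it through.** **Inputs.** Ablation on day 1; Visit 2 at day 90 with a window of ± 45 days (Table 1). Pain for up to 14 days after the procedure (section 2.3.3). For the illustration: n = 20 and a per-patient probability of 0.1 (section 2.2).

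**The gap.**
- Visit 2 window: 90 − 45 = day 45, to 90 + 45 = day 135.
- Time since ablation on day 1: 45 − 1 = 44 days, to 135 − 1 = 134 days; divided by 7, that is 6.3 to 19.1 weeks.
- End of the stated pain period: day 1 + 14 = day 15.
- From the end of that period to Visit 2: 45 − 15 = 30 days at the earliest, 90 − 15 = 75 days nominally, 135 − 15 = 120 days at the latest.

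No permitted date for Visit 2 falls inside the two weeks. The mismatch comes from the schedule itself and does not depend on how late a patient attends.

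**The plan's own safety figure.** Section 2.2 gives a probability of at least 0.9 that a problem with probability 0.1 occurs in at least one of 20 patients. The formula is 1 − (1 − p)^n, and 1 − 0.9^20 = 0.878, slightly below the stated value. That shortfall is a separate matter and nothing here depends on it. It serves only as the full-capture baseline below.

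**Illustration of incomplete capture.** Let q be the share of such events still reported at Visit 2. The documents give no value for q; those below are assumptions. The probability of recording at least one event is 1 − (1 − 0.1q)^20.

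| Assumed q | Calculation | Probability |
|---|---|---|
| 1 | 1 − 0.90^20 | 0.878 |
| 0.9 | 1 − 0.91^20 | 0.848 |
| 0.7 | 1 − 0.93^20 | 0.766 |
| 0.5 | 1 − 0.95^20 | 0.642 |

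These values apply to an event with a true rate of 10%. The article gives no such rate for pain or bleeding. For a common event the chance of seeing at least one case hardly moves: with an assumed 50% incidence and q = 0.5, 1 − 0.75^20 = 0.997. What suffers then is the estimated rate, which would be 25% instead of 50% (0.5 × 0.5), together with severity and duration.

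**The case against.** The strongest reply is that this is an article, and that a diary, a telephone call or a rule for unscheduled contacts may stand in the full protocol, which is not shown. The article does not say how events are elicited, so retrospective questioning is an inference. Participants also attend clinics that provide HIV care or regular follow-up, so notes from other contacts may exist. This stands as a limit on certainty. It does not remove the point, because the article prints a visit schedule with an adverse-event row and says data are collected at each visit, and those printed times miss the pain period.

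Several stronger readings are tempting, and the document does not support them:
- **That the safety data as a whole rest on recall.** Serious events are documented from consent to trial end, day-1 events are assessed at Visit 1, and lasting harms such as stenosis or textural change can be found by examination and anoscopy at Visits 2 and 3.
- **That all expected harms resolve within two weeks.** The duration attaches clearly only to pain; none is clearly given for bleeding or textural change.
- **That no patient is seen before Visit 2.** Staged ablation, usually within 3 months, may bring some back earlier, although Table 1 marks no adverse-event assessment for it.
- **That only intervention-related events are collected.** One sentence in section 2.2.4 reads that way, but the rows in Tables 1 and 2 are unqualified.
- **That the result is biased in favour of this device.** There is no comparator, the Discussion says performance against another device is unknown, and discomfort is not a named endpoint. Assessment by an unblinded physician is inherent in a declared open-label pilot.
- **That biopsy and ablation harms cannot be separated.** At least six biopsies at Visit 2 can cause pain or bleeding reported at Visit 3, but collection by visit already allows a split. It only needs to be tabulated.

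**Conclusion.** The point holds for non-serious, short-lived adverse events, chiefly pain and probably minor bleeding. On the printed schedule they are first assessed after the procedure day 44 to 134 days after ablation, at least about 30 days beyond the stated pain period. Their occurrence, severity and duration are therefore likely to be under-recorded.

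The timing rests only on figures in the article. The under-recording rests on two assumptions: that the full protocol adds no earlier collection, and that transient events are less completely reported weeks later. Its size is unknown; 0.766 and 0.642 illustrate assumed capture of 70% and 50% and are not estimates. This is a weakness in the timing of data collection that is cheap to mend and worth mending before enrolment. It does not invalidate the safety evaluation.

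**What to change.** Add one row to Table 1 for a one-page patient diary, with a daily pain score and bleeding for days 1 to 14, handed out at Visit 1 and collected at Visit 2. If the full protocol already provides for this, show it in the table.

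State that all adverse events are recorded, with relatedness to the ablation as a separate field. This settles the difference between the sentence in section 2.2.4 and the unqualified rows in Tables 1 and 2. In the safety tables, report events before the first follow-up biopsy separately from those after it.

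The cost is minor patient burden and a little data entry for 20 patients. No extra visit, staff or procedure is needed, and no treatment rule changes.
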